### Statistical methods

Each patient’s allocation to the analysed population will be defined prior to the analysis and will be documented. In the full-analysis set, patients will be analysed as randomized according to the intention-to-treat principle. The intention-to-treat principle implies that the analysis includes all randomized patients. The per-protocol analysis set will include all the patients without major protocol deviation. Deviations from the protocol will be assessed as major or minor. Patients with major deviations from the protocol will be excluded from the per-protocol analysis. The safety analysis set will analyse patients according to the treatment.

The null hypothesis assumes that the risk of development of POPF and postoperative complications is equal in both groups. A binary logistic regression will be applied in order to compare POPF in the groups adjusting for other factors. Two-tailed *t*-tests or nonparametric Mann–Whitney *U* tests will be applied for continuous secondary endpoints. χ^2^ tests or Fisher’s exact test will be used for analysis of categorical secondary endpoints. A *P*-value <0.05 will be considered statistically significant. Statistical analyses will be performed using NCSS statistical software (NCSS, Kaysville, UT, USA).

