### Study population and eligibility criteria

The DRAPA trial will encompass two participating centres: University Hospital Hradec Králové and University Hospital Olomouc, both in the Czech Republic. All patients who are scheduled for pancreatic resection at the two participating centres will be screened and assessed for eligibility.

Only patients who undergo pancreaticoduodenectomy or distal pancreatic resection will be included in the study. Patients with nonstandard procedures or a procedure associated with higher morbidity will be excluded from the study to achieve a homogeneous study group. Detailed inclusion and exclusion criteria are described below.

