### Postoperative data collection

A daily visit of the study patients will be made by clinical investigators or a delegated physician. All protocol-required information collected during the trial will be entered into the patient’s record form. Preoperative data gathered include patient sex, age, body mass index, American Society of Anesthesiologists physical status classification system score and comorbidities, especially those considered to increase the risk of POPF (diabetes mellitus and ischaemic heart disease) [35,36]. Intraoperative data to be collected include surgery duration, estimated blood loss, diameter of the main pancreatic duct and pancreatic gland texture. The diameter of the main pancreatic duct will be measured with a set of probes. Postoperative data to be gathered include volume of the drain output measured every 24 hours, amylase content analysed every other day starting on day 3, and the day of drain removal. Laboratory tests will include serum amylase, C-reactive protein, bilirubin and leukocyte count on days 3 and 7 [37]. Postoperative course assessments will include duration of intensive care, hospital stay including readmissions for postoperative complications, reinterventions (reoperations, endoscopy and interventional radiology procedures) and the reasons for readmissions. All the patients will have undergo ultrasonography or computed tomography (CT) before discharge from the hospital to detect any fluid collections. The patients will be seen by a clinical investigator 6 weeks and 3 months after the surgery in the outpatient department.

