### Methods for avoiding bias

#### Minimizing systemic bias

Patients will be randomized to one of the drain groups during the surgical procedure after resectability of the tumour is confirmed. Randomization will be accomplished using balanced permutation blocks by generation of random numbers in order to obtain homogeneity between groups. Patients scheduled for pancreaticoduodenectomy and distal pancreatectomy will be randomized separately, as these two procedures are different with regard to the course and consequences of POPF [25,44]. Opaque, sealed envelopes will be produced, labelled with the randomization number and containing a sheet that states the group allocation for the patient. Randomization envelopes will be used in consecutive order. Basic characteristics of the patient and the day of randomization will be documented on a data sheet so that compliance to the randomization scheme may be checked retrospectively. If patients are excluded from the study after randomization, their numbers will not be reused. Obviously, operating surgeons, attending physicians and nursing staff cannot be blinded, as the drains look different. However, outcome assessors will be blinded. The randomization process will follow the CONSORT guidelines (Figure 1) [45].

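### Randomisation is separate for pancreaticoduodenectomy and distal pancreatectomy, but the secondary tests are unstratified and the primary model does not commit to including procedure

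*Protocol article*

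**What the plan says.** All places are in the protocol article.

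- **Minimizing systemic bias.** Allocation takes place during surgery, in permuted blocks: "Randomization will be accomplished using balanced permutation blocks by generation of random numbers in order to obtain homogeneity between groups". The two procedures have separate allocation: "Patients scheduled for pancreaticoduodenectomy and distal pancreatectomy will be randomized separately, as these two procedures are different". The difference meant is in how POPF runs and what follows from it. Stratification by centre is not mentioned.
- **Study population and eligibility criteria.** "The DRAPA trial will encompass two participating centres".
- **Statistical methods, primary endpoint.** "A binary logistic regression will be applied in order to compare POPF in the groups adjusting for other factors". The factors are not named.
- **Statistical methods, secondary endpoints.** Continuous endpoints get two-tailed t-tests or Mann–Whitney tests. For the others, a chi-square test or Fisher's "exact test will be used for analysis of categorical secondary endpoints". No stratification or adjustment is attached to any of these tests.
- **Sample size calculation.** POPF is expected in 35% with the passive gravity drain and 17.5% with closed suction, with 97 patients per group. No rate is given by procedure.

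**The concern.** When randomisation is balanced within strata that predict the outcome, part of the outcome variation is removed from the comparison between arms by design. An analysis that ignores the strata still counts that variation in its standard error. The error is then too large for the design, the test rejects less often than its nominal level, and power is lost. The trial's own reason for separating the procedures is that POPF behaves differently in them, so by its own account procedure is the first variable that belongs in the analysis.

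For the secondary endpoints, the article names tests that leave procedure out. For the primary endpoint, it leaves open whether procedure is in the model. This also affects what is estimated: an odds ratio adjusted for a prognostic factor is a different quantity from the unadjusted one, even when the arms are perfectly balanced.

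**Working it through.** **1. The plan's own figure.** Inputs from Sample size calculation: 35% and 17.5%, α = 5%, power 80%. With the arcsine formula, h = 2·arcsin√0.35 − 2·arcsin√0.175 = 0.4029, and n = 2·[(1.96 + 0.8416)/0.4029]² = 96.7, so 97 per group. The unpooled formula gives 96 and the pooled formula 99, all two-sided. Power at 97 per group is 79.6% (two-sided, pooled). The figure therefore stands as a two-sided calculation. Read as one-sided, which is how the article labels it, the pooled formula gives 78. That label is a separate matter, and nothing below depends on it. The calculation makes no allowance for procedure.

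**2. Why ignoring the stratum is conservative.** Assume 97 per arm, of whom 63 have pancreaticoduodenectomy (PD) and 34 distal pancreatectomy (DP), a mix of about 65/35. The article gives no mix. Let a and b be the POPF rates in PD and DP, equal in both arms under the null, and let p = (63a + 34b)/97.

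- Variance per patient used by the unstratified test: V = p(1 − p).
- Variance per patient when the arms are balanced within procedure: W = [63a(1 − a) + 34b(1 − b)]/97.
- Actual type I error ≈ P(|Z| > 1.96/√(W/V)).

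Example with a = 25%, b = 53.5%: p = 33.94/97 = 0.350; V = 0.2275; W = (11.81 + 8.46)/97 = 0.2090; √(W/V) = 0.9585; 1.96/0.9585 = 2.045; type I error 0.041. In the same way, 30%/44% gives 0.048 and 20%/63% gives 0.030. W never exceeds V, so the error can only be in the conservative direction.

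**3. Simulation.** 200,000 trials per scenario, balanced within procedure, with a common odds ratio chosen so that the suction arm has 17.5% overall. The unstratified chi-square test is compared with a Cochran–Mantel–Haenszel (CMH) test stratified by procedure, both two-sided.

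| Assumed control rate PD / DP | Common OR | Type I: unstratified | Type I: CMH | Power: unstratified | Power: CMH |
|---|---|---|---|---|---|
| 35% / 35% | 0.394 | 0.051 | 0.049 | 80.1% | 80.0% |
| 30% / 44% | 0.389 | 0.048 | 0.050 | 80.0% | 80.2% |
| 25% / 53.5% | 0.367 | 0.042 | 0.050 | 81.0% | 82.8% |
| 20% / 63% | 0.328 | 0.030 | 0.050 | 82.6% | 86.7% |

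The simulated type I errors agree with step 2. The power gain from stratifying runs from nil (80.0 − 80.1 = −0.1 points) to 86.7 − 82.6 = 4.1 points. Monte Carlo error on power is about √(0.8·0.2/200,000) = 0.1 points.

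**4. Logistic regression.** A second simulation used a Wald test on treatment with 30% DP (assumed) and 3,000 trials per scenario. Adding procedure moved power from 80.7% to 82.2% when the procedure odds ratio was 3, and from 80.4% to 80.8% and from 80.6% to 81.2% when it was 2. Monte Carlo error here is about 0.7 points, so these results fit the lower part of the range in step 3.

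**5. The estimand.** The unadjusted odds ratio is (0.175/0.825)/(0.35/0.65) = 0.394. The table shows that the procedure-adjusted odds ratio for the same overall rates runs from 0.394 down to 0.328. Whether procedure is in the model therefore changes the number reported, as well as its precision.

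**The case against.** The strongest reply is that the primary model is already an adjusted one, that a covariate list is commonly left to the full protocol or SAP, and that neither is shown. This stands as far as it goes: a reader might infer that procedure is left out of the primary model, and the text does not show that. It shows only that inclusion is not committed. The reply does not cover the secondary endpoints, where the article does choose the tests and chooses unstratified ones. Those tests remain valid, so what is lost there is efficiency.

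Several stronger readings are tempting but not supported.

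- **Centre as a stratum.** "Randomization envelopes will be used in consecutive order" might suggest one envelope series per hospital. The article does not say so, and leaving centre unnamed contradicts nothing.
- **Gland texture and duct diameter as the key omitted predictors.** The article lists "diameter of the main pancreatic duct and pancreatic gland texture" among the intraoperative data and does not rank them. The only comorbidities it singles out as raising POPF risk are diabetes and ischaemic heart disease. Allocation is also intraoperative, and the article does not say that texture and duct are rated first.
- **Adjustment for post-allocation variables.** Drain volume, day of drain removal and C-reactive protein are recorded, but nothing suggests that they would enter the model.
- **Dilution of biliary leak by distal resections.** Patients without a biliary anastomosis add zeros to both arms. The risk difference shrinks, but so does its standard error. With assumed counts of 7/68 against 2/68, z = 1.72; with 29 event-free distal patients added per arm, 7/97 against 2/97, z = 1.71.

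**Conclusion.** The point holds in a limited form. The design separates the procedures for a stated reason, the named secondary tests ignore that separation, and the primary model does not commit to it. Any inference that false positives are at risk would be wrong, because the tests are conservative. The loss is about 0 to 4 percentage points of power, and the upper end needs control rates as far apart as 20% and 63%. With rates of 30% and 44% it is about 0.3 points (80.25% − 79.95%).

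These sizes rest on an assumed procedure mix, assumed procedure-specific rates, a common odds ratio and near-exact balance within procedure. They are worked at the planned POPF rates. The direction carries over to the secondary endpoints, but the size there cannot be given, since the article states no rates for them. The harm is small, but it can be avoided at almost no cost, and a specific better method exists.

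**What to change.** - **Primary endpoint.** State that the logistic regression contains drain type and procedure as fixed terms. Add centre if envelopes are kept per centre, and say whether they are. Limit any further covariates to a short named list recorded before allocation. Include gland texture or duct diameter only if they are documented as rated before the envelope is opened.
- **Secondary endpoints.** Replace the unstratified tests with procedure-stratified ones: Cochran–Mantel–Haenszel for categorical and van Elteren for ordinal or skewed endpoints, or models adjusted for procedure.
- **Timing and cost.** Trial status describes recruitment as ongoing, so this can still be fixed before the data are compared by arm. Procedure is known for every patient from the randomisation itself. No extra patients or data are needed, only wording and slightly more analysis work.

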## Discussion

Despite growing evidence in favour of pancreatic resection without intraabdominal drainage [13], routine elimination of drains cannot be recommended [25]. Rather more, drains could diminish the rate and severity of POPF in patients with high risk of POPF. Drains could possibly be avoided in patients with low risk of POPF [46]. However, the majority of pancreatic surgeons still consider routine placement of intraabdominal drains mandatory [15-17]. Once a decision is made to use intraabdominal drains, a controversy remains about which type of drain is most suitable in pancreatic resection [47]. Two types of drains are commonly used nowadays: passive gravity drains [26,30] and closed-suction drains [28,29]. Closed-suction drains are more effective, as they remove fluid from the abdominal cavity under light negative pressure [13]. However, some surgeons believe that closed-suction drains represent a potential hazard to patients [33] and that negative pressure might increase the risk of POPF [13]. No study conducted to date has specifically addressed the question of which type of drain is most beneficial for patients [12,13].

The DRAPA trial is designed to compare closed-suction drains with passive gravity drains in pancreatic surgery. Using the ISGPF definition of POPF will allow us to compare the results of this trial with those of other trials of drains in pancreatic surgery. This trial can show whether closed-suction drains represent hazards to patients or are beneficial in terms of decreasing POPF rates.

## Trial status

The DRAPA trial is currently recruiting patients. The last patient is expected to be recruited by December 2015.

## Abbreviations

CK-MB: Creatine kinase MB fraction
CONSORT: Consolidated Standards of Reporting Trials
DRAPA: DRAins in PAncreatic surgery trial
ECG: Electrocardiogram
ISGLS: International Study Group of Liver Surgery
ISGPF: International Study Group of Pancreatic Fistula
ISGPS: International Study Group of Pancreatic Surgery
POPF: Postoperative pancreatic fistula
WBC: White blood cells
